## Abstract

**Background:**

Adolescent HIV patients face enormous difficulty in accessing HIV care services. Given their vulnerability to risk-taking behaviour, this group also have worse treatment outcomes compared to other age groups. Poor treatment outcomes will impact negatively on HIV/AIDS management and control particularly in sub-Saharan Africa (SSA) as more than eight out of ten of the world’s HIV-infected adolescents live in this region of the world. Limited evidence exists on the effectiveness of service delivery interventions to support adolescents’ retention on antiretroviral therapy (ART) and adherence to ART. This trial is designed to evaluate the impact of conditional economic incentive and motivational interviewing on adolescents’ retention in HIV care and adherence to ART in Anambra State, Southeast Nigeria.

**Methods/design:**

The study will be a cluster randomised controlled trial that will be conducted in selected HIV treatment hospitals in Anambra State, Nigeria. Based on sample size calculation, 12 HIV treatment hospitals from Anambra will be selected for the study. Six HIV treatment hospitals each will be randomised to either the intervention or the control arm. A structured adherence support scheme termed the ‘Incentive Scheme’ will be applied to the intervention arm while the control arm will receive routine HIV care (usual care). Additionally, patients in the intervention arm will receive motivational interviewing at baseline and following initiation of antiretroviral therapy (ART), they will receive a gift voucher of US$5.6 when HIV viral load (VL) is < 20 copies/mL at 12 weeks, a gift voucher of US$2.8 if the VL remains suppressed for the next 3 months, and the next 6 months, and finally a gift voucher of US$5.6 if the VL remains < 20 copies/mL at 1 year. All gift vouchers will be conditional not only on VL results but attending the motivational interviews. The primary outcome for the trial will be the difference between groups in the proportion with HIV VL suppression (≤ 20 copies/mL) by 12 months and then 24 months after withdrawal of incentive.

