### Trial design

The study will be a cluster randomised controlled trial. Clusters are HIV treatment hospitals in Anambra state. Hospitals (the clusters) will be matched by type of hospital (e.g. secondary or tertiary) and the paired units will be randomly assigned to the intervention or the control arm. The trial has two periods – intervention period and post-intervention period. Each of these periods will run for a 1-year duration. Further details of the trial are shown in Tables 1 and 2 and Additional file 1. Figure 1 shows the schedule of enrolment, interventions and assessments for the trial design.

**Table 1 Tab1:** The World Health Organisation (WHO) trial registration dataset

Data category	Information
Primary registry and trial identifying number	The Pan African Clinical Trials Registry: https://pactr.samrc.ac.za/ (PACTR201806003040425)
Date of registration in primary registry	2 February 2018
Source of monetary or material support	European Developing Countries Clinical Trial Partnership (EDCTP)
Primary sponsor	Nnamdi Azikiwe University
Contact for public queries	[contact]
Public title	Conditional Economic Incentive and Motivational Interviewing to Improve Adolescents’ Retention and Adherence to Antiretroviral Therapy and Care in South East Nigeria: a Cluster Randomised Trial
Scientific title	Conditional Economic Incentive and Motivational Interviewing to Improve Adolescents’ Retention and Adherence to Antiretroviral Therapy and HIV Care in South East Nigeria: a Cluster Randomised Trial
Country of recruitment	Nigeria
Health condition or problem studies	HIV
Interventions	Conditional economic incentive and motivation interviewing
Key inclusion criteria	All patients with HIV who had transitioned from pediatric stage to a young person/adult; age 10–19 years irrespective of CD4+ cell count; currently off antiretroviral therapy (ART) despite multiple attempts to restart; willing to restart therapy and sign a patient agreement
Study type	Interventional
Date of first enrolment	Yet to commence
Target sample size	240
Recruitment status	Yet to commence
Primary outcome	HIV viral load
Key secondary outcome	CD4+ count, adherence to ART (measured using pill count) and adherence to appointment with hospital

**Table 2 Tab2:** Protocol for conditional economic incentives

Started ART	VL response and attended for MI	Voucher value (USD)
Week 12	VL < 20	5.6
6 months suppressed	Sustained VL < 20	2.8
9 months suppressed	Sustained VL < 20	2.8

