### Intervention

A structured adherence support scheme termed the ‘Incentive Scheme’ will be applied to the intervention hospitals while the control hospitals will receive usual care. The Incentive Scheme added to the usual care involves financial incentives linked to viral load (VL) combined with attendance for motivational interviewing (MI) with an adherence counsellor trained in MI techniques. (Table 2) [14]. Training on MI will be in accordance with an MI guide that covers key points for MI as well as examples and key insights to assessing patient risk, risk reduction counselling and inspiring behaviour change [16]. Participants in hospitals randomised to usual care will receive the normal care obtainable in the HIV treatment hospitals. This typically involves monthly or bi-monthly scheduled hospital visit for medical examination, prescription refill and adherence counselling, bi-yearly VL assessment, and yearly CD4^+^ count analysis.

In addition to the usual care, participants in the intervention hospitals will receive MI at baseline and following initiation of ART, they will receive a gift voucher of US$5.6 when VL < 20 copies/mL at 12 weeks, a gift voucher of US$2.8 if the VL remains suppressed for the next 3 months, and the next 6 months, and finally a gift voucher of US$5.6 if the VL remains < 50 copies/mL at 1 year. All incentives will be conditional not only on patients meeting their VL target but attending for MI. Those with VL higher than the thresholds will not receive the incentive. The potential maximum cumulative financial incentive is US$16.8 if viral suppression is sustained for 12 months. The patient will have the liberty to withdraw from the scheme at any time point. Routine hospital data will be collected and outcomes will be assessed by changes in HIV VL and CD4+ count from baseline, at 12 months from enrolment and at 24 months to establish whether any benefit is seen from the intervention could be sustained when financial incentives cease. Each patient in the study will be assigned to a study nurse working in the HIV treatment hospital and they will be tracked with their mobile phone numbers.

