### Outcomes

The primary outcome for the trial will be the difference between groups in the proportion with HIV VL suppression (≤ 20 copies/mL) by 12 months and 24 months. The secondary outcome measure will include the average change in CD4+ count, adherence to ART (measured using pill count) and adherence to an appointment with the hospital for individual participants. Viral load analysis will be done using the COBAS TaqMan 96 and the Amplilink software.

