### Sample size

The sample size was calculated using a web-based sample size calculator of the UCSF Clinical and Translational Science Institute [17]. The sample size calculation is based on the proportion of patients with VL suppression ≤ 20 copies/mL – the main outcome measure. Based on a power of 80% and an α of 0.05 (two-sided), 63 patients per group will be needed to observe a 12% (assumed standard deviation of 24%) increase in the number of participants with VL suppression as previously reported [18]. After adjustment for the cluster design, based on the assumed intracluster correlation coefficient of 0.047 and a fixed cluster per arm of six HIV treatment hospitals, the effective sample size increased to 120 patients per arm (i.e. a total of 240 participants). Due to potential attrition that could arise as a result of severe adverse events, treatment failures or the participant simply deciding to withdraw, we added three participants per hospital increasing the number of participants in each arm to 138 (i.e. a total of 276 participants). A fixed number of six clusters or hospitals per arm (i.e. 12 hospitals in total for the trial) were informed by the fact that only 12 hospitals in Anambra State offer comprehensive HIV services including HIV-adherence counselling and antiretroviral treatment services and these 12 hospitals have appreciable HIV client load. Each of the hospitals will, therefore recruit 23 participants.

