### Statistical analysis

Statistical analysis will be conducted using IBM SPSS for Windows, Version 20 (IBM Corp, Armonk, NY, USA). As shown in Table 3, descriptive statistics will be used to evaluate differences in demographic and clinical characteristics. Categorical variables will be expressed as frequencies or percentages and quantitative variables as means and standard deviations or medians and interquartile ranges. An intention-to-treat analysis will be conducted. A secondary per-protocol analysis will also be conducted. The latter will include only those participants who completed the treatment protocol originally allocated, providing results on the efficacy of the trial. If there is a significant difference between the intention-to-treat analysis and the per-protocol analysis, then the former will be reported. Comparison of dichotomous measurements between the intervention group and the control group will be conducted using the chi-square test (or Fisher’s exact test) while comparison of the mean of continuous measurements between the intervention group and the control group will be conducted using an independent *t* test. A two-sided *p* value of 0.05 will be used to indicate statistical significance.

**Table 3 Tab3:** Data analysis outline

Study objective	Outcome variable	Type of analysis
Objective 1: effectiveness of intervention	Primary outcome	
	HIV viral load	*χ*^2^ test or Fisher’s exact test
	Secondary outcomes	
	CD4+ count	Within group: paired-sample *t* tests or Wilcoxon signed-rank tests; between group – Student’s *t* test or Wilcoxon signed-rank tests
	Adherence to antiretroviral therapy (ART)	*χ*^2^ test or Fisher’s exact test
	Adherence to hospital appointment	Within group: paired-sample *t* tests or Wilcoxon signed-rank tests; between group – Student’s *t* test or Wilcoxon signed-rank tests
Objective 2: cost-effectiveness analysis	Cost-effectiveness of intervention	Incremental cost-effectiveness ratio
Objective 3: qualitative assessment of implementer’s perspective	Programme implementer’s perspective	In-depth interview (thematic content analysis)

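### The primary outcome covers two time points under one 0.05 threshold and a sample size for one comparison, and the abstract, read literally, dates the second a year later than the Methods

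*Protocol article*

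**What the plan says.** The following places in the protocol article bear on this point.

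- **Abstract, Methods/design:** the primary outcome is the between-group difference in the proportion suppressed, "by 12 months and then 24 months after withdrawal of incentive".
- **Outcomes:** the same outcome is given as "by 12 months and 24 months", with no reference to withdrawal.
- **Trial design:** there is an intervention period and a post-intervention period. "Each of these periods will run for a 1-year duration".
- **Intervention and Table 2:** the last voucher falls at 12 months. Outcomes are assessed "at 12 months from enrolment and at 24 months to establish whether any benefit" lasts once the incentives cease.
- **Statistical analysis and Table 3:** a two-sided p "value of 0.05 will be used to indicate statistical significance". Table 3 gives the viral load outcome one line, a chi-square or Fisher's exact test, without a time point.
- **Sample size:** "Based on a power of 80% and an α of 0.05 (two-sided), 63 patients per group will be needed", raised to 120 per arm for clustering and 138 per arm for attrition. No time point is named.

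None of these places ranks the two time points, divides the 0.05 between them, or says whether one or both must be significant.

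**The concern.** The two time points answer different questions. Month 12 measures the effect while incentives are being paid; month 24 measures whether it lasts after they stop. The protocol itself expects that the answers may differ: its theoretical section says that incentives may help in the short term without a lasting effect. A positive result at 12 months with a null result at 24 months is therefore foreseeable, and the article does not say whether such a trial has met its primary outcome.

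The design figures were set for one test. Once two tests share the primary label, either the 5% error rate or the 80% power has to give way, depending on the success rule.

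The date of the second assessment matters for the same reason. If it cannot be read the same way in the abstract and the Methods, the primary outcome is not fully fixed.

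**Working it through.** **Inputs.** From Sample size: difference 12%, SD 24%, two-sided alpha 0.05, power 80%, intracluster correlation 0.047, six hospitals per arm. From Outcomes: two time points. From Statistical analysis: 0.05 for every test. The correlation between the two test statistics is not given, so a range is assumed. The plan's effect size and SD are taken at face value.

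**1. Reproduce the plan's own figure.**

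- Unadjusted: n = 2 × [0.24 × (1.960 + 0.842) / 0.12]² = 62.8, rounded up to 63 per group. This matches.
- Patients per hospital with six hospitals fixed: m = n(1 − ICC) / (k − n × ICC) = 63 × 0.953 / (6 − 63 × 0.047) = 60.04 / 3.039 = 19.76, rounded up to 20. Then 20 × 6 = 120 per arm. This matches.
- Attrition: (20 + 3) × 6 = 138 per arm. This matches.

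The arithmetic is sound, and it covers exactly one test at 0.05.

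**2. If either time point suffices.** Familywise error = 1 − P(|Z₁| < 1.96 and |Z₂| < 1.96), with Z₁ and Z₂ bivariate normal with correlation r. At r = 0 this is 1 − 0.95² = 0.0975.

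**3. If both are required.** Take the planned 12% difference to be present at both time points and 63 effective patients per group. The expected test statistic is (0.12 / 0.24) × √(63 / 2) = 2.806. Joint power = P(both Z > 1.96), the bivariate normal probability with both limits at 2.806 − 1.960 = 0.846. At r = 0 this is 0.801² = 0.642.

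| Assumed r | Familywise error, either suffices | Joint power, both required |
|---|---|---|
| 0 | 9.8% | 64% |
| 0.3 | 9.5% | 67% |
| 0.5 | 9.1% | 69% |
| 0.7 | 8.3% | 71% |
| 0.9 | 7.0% | 75% |

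**4. Cost of splitting alpha equally.** At 0.025 per time point, n = 77 per group and m = 77 × 0.953 / (6 − 77 × 0.047) = 30.8, rounded up to 31. That is 186 per arm, or 204 with three extra per hospital. Kept at 120 per arm (effective size 120 / 1.893 = 63.4, where 1.893 = 1 + 19 × 0.047), power per time point falls from about 80% to about 72%.

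**5. Timing.** Incentives end at month 12. The abstract's wording, taken literally, gives 12 + 24 = month 36. Two one-year periods give 12 + 12 = month 24. The two readings differ by 12 months, and month 36 lies outside the follow-up that the Trial design section describes.

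**The case against.** Four arguments can be made on the other side.

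- **Success rules often sit in the analysis plan, which is not shown.** This has weight: the lack of a multiplicity rule would not be a finding by itself. But the article itself fixes two primary time points, one threshold and a size for one comparison. Those three statements do not fit together under either success rule.
- **The either-suffices rule is inferred.** A reader might conclude that the protocol lets the trial claim success on either time point. It does not say so; its wording can equally mean that both are needed, in which case error is not inflated and the cost is power. This objection stands, and the conclusion is therefore stated for both rules.
- **The inflation is easily overstated.** The same participants in the same hospitals are measured twice, so independence is implausible and 9.8% is an upper bound. A reader might also combine the two time points with the unadjusted chi-square test. With design effect 1.893 that test has a true level of about 15.4%, and 1 − (1 − 0.154)² = 28%. That figure again assumes independence, and most of it is the separate clustering problem, which settling the time points would not repair. It does not belong here.
- **The timing conflict is confined to the abstract.** A reader might infer that follow-up will run to month 36. Trial design, Intervention and Outcomes give no support for that, and the likely intent was month 24, which falls after withdrawal. It is also true that the Intervention section attaches the enrolment origin only to the 12-month visit; counting month 24 from enrolment is an inference from the two one-year periods, though a firm one. The objection lowers the weight of the timing point but does not remove it.

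A reader might further suppose that the registry entry needs correcting. The registration data in Table 1 list the primary outcome only as viral load, with no time point, so nothing visible supports that.

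**Conclusion.** The concern holds in two parts.

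First, for the primary outcome as defined, the stated 5% error and 80% power cannot both be true. If one time point is enough, the familywise error is about 7% to 9.5% (assumed correlation 0.9 to 0.3). If both are needed, joint power is about 64% to 75% (assumed correlation 0 to 0.9). The power range assumes the planned difference at both time points; if the effect fades after incentives stop, joint power is lower. The sample size arithmetic is not at fault.

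Second, the abstract's literal month 36 conflicts with the month 24 implied by the Methods. This is most likely a drafting slip, but it concerns the timing of the primary outcome.

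**What to change.** - **Outcomes and Statistical analysis:** test the two time points in fixed order. Test suppression at 12 months from enrolment first, at two-sided 0.05. Test suppression at 24 months from enrolment at two-sided 0.05 only if the first test is significant. This holds the familywise error at 0.05 and leaves the size at 120 per arm before attrition.
- **Sample size:** say that the calculation refers to the 12-month comparison.
- **Abstract:** give the second time point as 24 months from enrolment, which is 12 months after withdrawal of the incentive, and use the same time origin in Intervention and Outcomes.

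The cost is a change of wording. The downside is that the 24-month durability result cannot support a confirmatory claim on its own if the 12-month test fails. Nor does the ordering raise the chance of succeeding at both time points, which stays at about 64% to 75% under the assumptions above. Other rules would also resolve the ambiguity. An equal alpha split would need about 186 per arm before attrition, and requiring both would mean accepting that lower joint power or enrolling more. With only 12 hospitals available, fixed order is the least costly. The choice should be made before outcome data accrue.

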**Discussion:**

The findings of this proposed trial will provide evidence on the feasibility of applying conditional economic incentives combined with motivational interviewing to improve retention and adherence to antiretroviral therapy of adolescents living with HIV in Nigeria and possibly in other sub-Saharan African countries.

**Trial registration:**

Registered in the Pan African Clinical Trials Registry, ID: PACTR201806003040425. Registered on 2 February 2018.

**Electronic supplementary material:**

The online version of this article (10.1186/s13063-018-3095-4) contains supplementary material, which is available to authorized users.

## Background

Adolescent HIV patients face enormous difficulty in accessing HIV care services and they have worse treatment outcomes compared to other age groups [1]. Few studies have investigated HIV-infected adolescents’ progression through the HIV care pathway and have generally found their outcomes to be poor and worse than those for adults or young children. Specifically, rates of retention in care prior to antiretroviral therapy (ART) initiation, as well as retention and adherence to treatment after ART initiation, have been shown to be poor [2, 3]. Furthermore, a systematic review showed an average of only 62% of 12- to 24-year-olds achieved 95% or greater adherence to ART [4]. Poor retention in care and adherence to ART will impact negatively on HIV/AIDS management and control, particularly in SSA as more than eight out of ten of the world’s HIV-infected adolescents live in this region of the world [5].

Poor adherence in adolescents may be connected to the unique psychological, social and health needs that are particular to the adolescent stage. Adolescence is sometimes accompanied by a desire for self-discovery, an emerging sense of autonomy, separation from caregivers and the assertion of independence, the quest for recognition and acceptance, all of which could lead to risk-taking behaviour [6, 7]. Evolving interventions to support retention of HIV-infected adolescents in care as well as ensuring their adherence to ART is essential not only to improve individual health for persons living with HIV but also to reduce transmission.

There is limited evidence on the effectiveness of service delivery interventions to support adolescents’ linkage from HIV diagnosis to ART initiation, retention on ART and adherence to ART. A systematic review by Kim et al. identified a small number of studies that assessed the effectiveness of interventions to support adolescents’ linkage from HIV diagnosis to ART initiation, retention on ART and adherence to ART [4]. The systematic review concluded that offering individual and group education and counselling, financial incentives, increasing clinic accessibility and provision of specific adolescent-tailored services appear promising interventions and warrant further investigation.

### The theoretical basis for conditional economic incentive and motivational interviewing (MI)

There is a theoretical foundation potentially underlying conditional economic incentives (CEI) for HIV treatment adherence. Micro- and behavioural-economic framework suggest that non-adherence is attributed to the perception of reduced utility due to out-of-pocket costs, side effects, perceived risks, delayed benefits, or other idiosyncratic reason [8]. CEI, therefore, increases income when adherent, which in turn increases utility. Additionally, while people know that non-adherence to ART may risk treatment failure, opportunistic infections, etc., these events may occur in the future. Hence, CEI helps to bring the benefits (in monetary terms) much closer to the present.

In Nigeria, the conditional economic incentive has been applied in the Subsidy Reinvestment and Empowerment Programme (SURE-P) Maternal and Child Health (MCH) programme with the aim to increase demand and access to maternal and neonatal health services. In the programme, conditional cash transfer was used to encourage pregnant women from poor households to seek maternal and child health in public hospitals. Conditional cash transfer in a MCH context showed the capacity of having a significant effect on service uptake although the authors concluded that there is a need to track beneficiaries throughout the continuum of care [9].

If appropriately implemented, CEI could help improve patients’ adherence to HIV treatment in the short-term, while the incentives are in place. However, this does not necessarily create a lasting effect after the incentives are removed [8]. Social and behavioural theoretical perspectives explain how behaviour can become habitual and sustained [8]. For instance, the social context that supports satisfaction of basic needs support growth processes, including internally motivated behaviours [10–12]. Additionally, self-determination theory postulates that internalised motivation, rather than external incentives, is essential to long-term behavioural regulation. Therefore, interventions that help self-determination, such as MI, should be coupled to CEI in order to achieve a long-term adherence.

Motivational interviewing is a counselling method informed by self-determination theory and represents a general and practical approach for changing behaviours by enhancing and facilitating a patient’s own internally motivated change process [13]. MI recognises that responsibility for changing behaviour is assumed to lie within the individual, and ambivalence is recognised as a natural part of this change process [8]. MI is different from other adherence counselling technique currently applied in HIV care due to three key elements: MI fosters collaboration between the counsellor and the client; MI evokes or draws out the client’s ideas about change, and MI emphasises the autonomy of the client.

